### 6.3.2.2 OXALIPLATIN NON-HAEMATOLOGICAL TOXICITY

In Grade 3 or 4 stomatitis or diarrhoea reduce **Oxaliplatin** dose to 100mg/m^2.

Neurosensory toxicity:

The following dose reductions should be made:

| Toxicity                                       | ≤ 7 days          | > 7days                                                                            | Persisting until next cycle                                                                                    |
|------------------------------------------------|-------------------|------------------------------------------------------------------------------------|----------------------------------------------------------------------------------------------------------------|
| Cold-related dysaesthesia               | No dose reduction | No dose reduction                                                                  | Oxaliplatin until recovery then restart with 25% reduction of scheduled dose

Omit oxaliplatin if recurs |
| Paraesthesia without pain               | No dose reduction | No dose reduction                                                                  | Oxaliplatin until recovery then restart with 25% reduction of scheduled dose

Omit oxaliplatin if recurs |
| Paraesthesia with pain                  | No dose reduction | Delay oxaliplatin until recovery then restart with 25% reduction of scheduled dose | Omit Oxaliplatin                                                                                               |
| Paraesthesia with functional impairment | No dose reduction | Delay oxaliplatin until recovery then restart with 25% reduction of scheduled dose | Omit Oxaliplatin                                                                                               |

## 6.4 DOSE MODIFICATION FOR FOLFOX TOXICITY/5-FU MONOTHERAPY

| Toxicity
NCI CTC Grade                                                                                                                                                                                                                                                                                                                                                                                                                                                                                                                                                                    | Therapeutic
measures for
toxicity                                                      | Initial Doses (mg/m  /course)      |                                  |                               |
|----------------------------------------------------------------------------------------------------------------------------------------------------------------------------------------------------------------------------------------------------------------------------------------------------------------------------------------------------------------------------------------------------------------------------------------------------------------------------------------------------------------------------------------------------------------------------------------------|----------------------------------------------------------------------------------------------|------------------------------------------------|----------------------------------|-------------------------------|
|                                                                                                                                                                                                                                                                                                                                                                                                                                                                                                                                                                                              |                                                                                              | 5-FU bolus
400                              | 5-FU Infusion
1200 x 2        | Oxaliplatin
85             |
|                                                                                                                                                                                                                                                                                                                                                                                                                                                                                                                                                                                              |                                                                                              | Dose modifications (mg/m  /course) |                                  |                               |
| Neutrophils grade 3 or lower (<1.0x10  /l)                                                                                                                                                                                                                                                                                                                                                                                                                                                                                                                                       | Delay until ≥1x10  /L
Consider G-CSF for G4 neutropenia / febrile neutropenia | 400                                            | 1200                             | 85                            |
| Febrile neutropenia/ recurrent neutrophils grade 3 or lower (<1.0x10  /l), despite secondary prophylaxis                                                                                                                                                                                                                                                                                                                                                                                                                                                                         | Delay until ≥1x10  /L                                                            | Omit bolus                                     | 1200 (consider reduction to 900) | 85 (consider reduction to 70) |
| Platelets grade 2 (50-75 x10  /l)                                                                                                                                                                                                                                                                                                                                                                                                                                                                                                                                                | Delay until G1 (≥75x10  /l)                                                      | 400                                            | 1200                             | 85                            |
| Platelets grade 3/4 (<50x10  /l)                                                                                                                                                                                                                                                                                                                                                                                                                                                                                                                                                 | Delay until G1 (≥75x10  /l).
Consider emitting bolus 5-FU                     | 300 (consider omission)                        | 900                              | 65                            |
| Stomatitis or Diarrhoea grade 3                                                                                                                                                                                                                                                                                                                                                                                                                                                                                                                                                              | Sucralfate, Codeine
Loperamide, as indicated                                              | 300                                            | 900                              | 85                            |
| Stomatitis or Diarrhoea recurrent grade 3 or single grade 4                                                                                                                                                                                                                                                                                                                                                                                                                                                                                                                                  | Sucralfate, Codeine
Loperamide, as indicated                                              | 300                                            | 900                              | 70                            |
| PPE grade 3                                                                                                                                                                                                                                                                                                                                                                                                                                                                                                                                                                                  | Emollients                                                                                   | 300                                            | 900                              | None                          |
| Neuropathy                                                                                                                                                                                                                                                                                                                                                                                                                                                                                                                                                                                   |                                                                                              | None                                           | None                             | See section 6.3.2.2           |
| 
 
In all cases treatment should be delayed until recovery of toxicity to grade 2 (except thrombocytopenia, where recovery should be to grade 1 (≥75x10^9/L)). Omission of the bolus of 5-FU can be considered in cases of neutropenia and thrombocytopenia.
 
If a patient develops grade 4 neutropenia, delay chemotherapy until recovery to grade 2 (Neutrophils ≥1.0x10^9/l) and proceed with chemotherapy without any dose reductions for subsequent cycles with GCSF support on days 7-11 post chemotherapy.
 
 |                                                                                              |                                                |                                  |                               |

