## 5 RECOMMENDED 5-FU MONOTHERAPY REGIMEN (2 WEEKLY CYCLE)

5-FU/Folinic acid can be used if concomitant oxaliplatin is contraindicated

| Drug                                                                                                                                                                     | Dose                   | Day(s) in cycle | Administration                                   |
|--------------------------------------------------------------------------------------------------------------------------------------------------------------------------|------------------------|-----------------|--------------------------------------------------|
| Folinic acid a                                                                                                                                                | 400 mg/m   | 1               | 2 hr i.v. infusion concurrently with oxaliplatin |
| 5-FU                                                                                                                                                                     | 400 mg/m   | 1               | i.v. bolus                                       |
|                                                                                                                                                                          | 2400 mg/m  | 1-2             | 48 hr i.v. infusion b                 |
| a where local practice is to use levofolinic acid, then this is permitted at the locally approved dose
b or 46 hours if this is local practice. |                        |                 |                                                  |

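### The FOLFOX/5-FU dose-modification table prints per-day infusional 5-FU figures (1200 or 900) under a per-course unit, where the full course is 2400 mg/m2

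*Protocol*

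**What the plan says.** Protocol Appendix 2, sections 4 and 5 (the recommended FOLFOX and 5-FU monotherapy regimens), each give infusional 5-FU as 2400 mg/m2 over days 1-2 of a two-week cycle. It runs as a single infusion of 48 hours, or 46 where that is local practice.

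The table in section 6.4 has two header levels. The first, "Initial Doses (mg/m 2 /course", carries the column head "5-FU Infusion 1200 x 2", beside a 5-FU bolus of 400 and oxaliplatin of 85. The second, directly over the modification rows, is "Dose modifications (mg/m 2 /course". None of the infusion cells below it repeats the x 2; the febrile neutropenia row, for example, reads "1200 (consider reduction to 900".

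The first row covers neutrophils below 1.0 and includes the advice "Consider G-CSF for G4 neutropenia / febrile neutropenia". It prints 400, 1200 and 85. The note under the table says that after recovery from grade 4 neutropenia the site should "proceed with chemotherapy without any dose reductions for subsequent cycles with GCSF support".

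Separately, section 5 opens with "5-FU/Folinic acid can be used if concomitant oxaliplatin is contraindicated", but its table times the folinic acid as "2 hr i.v. infusion concurrently with oxaliplatin".

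**The concern.** Within one row, two columns (bolus and oxaliplatin) are true per-course doses and the third (infusion) is a per-day dose, while a single per-course unit is printed over all three. The regimen tables describe one continuous infusion of 2400, not two daily doses of 1200. A reader going from the regimen to a modification row therefore sees 2400 become 1200, which can pass for a deliberate halving.

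At stake is an underdose of an investigational product after toxicity. For poor responders in the intervention arm it could persist: Appendix 2, section 1.3 starts post-operative chemotherapy at the finishing dose of the pre-operative phase if that had been reduced.

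**Working it through.** **Inputs**, all from protocol Appendix 2: full infusion 2400 mg/m2 per cycle (sections 4 and 5); full bolus 400 (sections 4, 5 and 6.4); infusion header 1200 x 2 per course (section 6.4); row entries (section 6.4).

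**Step 1: the plan's own figure.** 1200 x 2 = 2400 mg/m2 per course. The 6.4 header and the regimen tables agree, so the full dose is not in doubt.

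**Step 2: the infusion cells.**

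| Row in 6.4 | Bolus | Infusion as printed | Literal share of 2400 | Share if x 2 |
|---|---|---|---|---|
| Neutrophils <1.0 | 400 | 1200 | 50% | 100% |
| Febrile or recurrent neutropenia | omitted | 1200 (optional 900) | 50% (37.5%) | 100% (75%) |
| Platelets grade 2 | 400 | 1200 | 50% | 100% |
| Platelets grade 3/4 | 300 (or omit) | 900 | 37.5% | 75% |
| Stomatitis/diarrhoea grade 3 | 300 | 900 | 37.5% | 75% |
| Same, recurrent grade 3 or single grade 4 | 300 | 900 | 37.5% | 75% |
| PPE grade 3 | 300 | 900 | 37.5% | 75% |

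The neuropathy row has no numeric infusion entry. That leaves seven numeric cells: three at 1200 and four at 900. The omission is uniform, so it is not a single misprint.

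**Step 3: which reading is meant.**

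- Bolus in the 900 rows: 300/400 = 75%. Infusion read per day: 900/1200 = 75%. Infusion read per course: 900/2400 = 37.5%. Only the per-day reading matches the bolus.
- In the neutrophil and platelet grade 2 rows, bolus 400 and oxaliplatin 85 are unchanged. A halved infusion there would be out of line with both.
- For grade 4 neutropenia the note under the table rules out any reduction. A literal 1200 per course contradicts it; 1200 x 2 does not.
- The 5-FU banding table (section 8) has rows for 900 and 1,200 mg/m2 and none for 1800 or 2400. Two banded 1,200 doses come within a few per cent of 2400 x BSA. The extremes are BSA 1.3 (2 x 1500 = 3000 against 3120, -3.8%) and BSA 2.0 and 2.2 (2 x 2500 = 5000 against 4800, and 2 x 2750 = 5500 against 5280, both +4.2%).

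All four checks support the per-day reading.

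**Step 4: total 5-FU per course, literal against intended.**

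- 400/1200 rows: 400 + 1200 = 1600 against 400 + 2400 = 2800; 1600/2800 = 57.1%.
- 300/900 rows (bolus kept): 300 + 900 = 1200 against 300 + 1800 = 2100; 1200/2100 = 57.1%.
- Febrile neutropenia row (no bolus): 1200 against 2400, or 900 against 1800 if reduced; 50% either way.

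For scale, Appendix 2, section 1 allows dose banding and capping only within 7% either side of the calculated dose.

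**The case against.** The strongest reply is that the table supplies its own key. The column is headed 1200 x 2, so each cell can be read against its header: bolus 400 stays 400, oxaliplatin 85 stays 85, infusion 1200 stays 1200 of 1200 x 2. The banding table uses the same daily quantities. The clash with the grade 4 neutropenia note arises only under the literal reading, so it is evidence of intent and not a second defect. Sections 1 and 6.2 of Appendix 2 make the doses and modifications reference guidance and let sites follow local protocols, and these are established regimens given under normal pharmacy procedures. A halved infusion would require a site to overlook the header, the regimen table, the paired columns and its own protocol.

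Most of this stands. The intent is recoverable and a dosing error is unlikely; the 50% and 37.5% figures measure a misreading, not what the protocol means to prescribe. It does not make the printed unit right. The second header restates per course immediately above the cells, and the banding table carries no per-day label that would settle the matter. A chemotherapy dose should not have to be inferred against its own unit.

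It is also fair that the folinic acid phrase in section 5 is a separate clerical leftover. Dose, day and duration are all stated, no dosing question follows, and it adds no weight.

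**Conclusion.** The point holds and is minor. Seven infusional 5-FU cells in section 6.4 carry a unit that makes them half of what is intended: 1200 against 2400 mg/m2 per course in three cells, and 900 against 1800 in four. That the figures are per day is an inference, but the header, the bolus ratio, the no-reduction note and the banding table all agree with it, so this is a labelling error and not an unresolved dose. Any error from following the print would be an underdose. Its likelihood is limited by the reference status of the table and by local practice. The recruitment-rate endpoint, sample size, error rates and analysis are untouched.

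**What to change.** In section 6.4 of Appendix 2, print 1200 x 2 and 900 x 2 (or 2400 and 1800) in the seven infusion cells, including the optional reduction in the febrile neutropenia row. Alternatively, relabel that one column as mg/m2 per day for two days and leave the cells as they are. In section 5, delete the reference to oxaliplatin from the folinic acid timing, leaving a two-hour infusion.

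The cost is seven cells or one column label, plus one phrase, at the next routine amendment. Design, data collection and analysis do not change.

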## 7 CONCOMITANT MEDICATIONS

- All treatments being taken by the patient on entry to the study or at any time during the interventional phase of the study in addition to the study treatments are regarded as concomitant treatments and must be documented on the CONCOMITANT MEDICATIONS CRF.
- Throughout the study, investigators may prescribe any concomitant medications or treatments deemed necessary to provide adequate supportive care EXCEPT FOR THOSE LISTED IN THE SECTION BELOW.

**Permitted, non-permitted medications and medications to be used with caution**

- Investigators should refer to the SmPC for each of the drugs used for details relating to contraindications, special warnings and precautions for use, and interactions with other medical products and other forms of interactions. Up to date versions of these are available at <http://emc.medicines.org.uk/>
- Live vaccines** (including inhaled flu vaccines) should not be administered to immunocompromised patients, including those receiving chemotherapy or within 6 months after receiving chemotherapy.

## 8 DOSE BANDING

Dose banding of all IMPs should be as per local practice. The following dose banding tables are for guidance only.

| Capecitabine (Xeloda®) Capsules (150mg, 500mg) – Daily Dose to be Divided     |                       |              |              |
|-------------------------------------------------------------------------------|-----------------------|--------------|--------------|
| Regimen                                                                       | BSA (m  ) | AM Dose (mg) | PM Dose (mg) |
| Capecitabine 2000mg/m^2
Per day in 2 divided doses | 1.3                   | 1000         | 1500         |
|                                                                               | 1.4 – 1.6             | 1500         | 1500         |
|                                                                               | 1.7 – 1.9             | 1500         | 2000         |
|                                                                               | 2.0 – 2.3             | 2150         | 2150         |
| Capecitabine 1700mg/m^2
Per day in 2 divided doses | 1.3                   | 1000         | 1150         |
|                                                                               | 1.4 – 1.6             | 1000         | 1500         |
|                                                                               | 1.7 – 1.9             | 1500         | 1500         |
|                                                                               | 2.0 – 2.2             | 1500         | 2000         |
|                                                                               | 2.3                   | 2150         | 2150         |
| Capecitabine 1300mg/m^2
Per day in 2 divided doses | 1.3 – 1.5             | 800          | 1000         |
|                                                                               | 1.6 – 1.7             | 1000         | 1150         |
|                                                                               | 1.8 – 2.1             | 1000         | 1500         |
|                                                                               | 2.2 – 2.3             | 1500         | 1500         |
| Capecitabine 1000mg/m^2
Per day in 2 divided doses | 1.3                   | 650          | 650          |
|                                                                               | 1.4 – 1.6             | 500          | 1000         |
|                                                                               | 1.7 – 1.9             | 800          | 1000         |
|                                                                               | 2.0 – 2.3             | 1000         | 1150         |

| Fluorouracil (25 and 50mg/mL, 2.5g vials) |    |      |      |      |      |      |      |      |      |      |      |      |
|-------------------------------------------|----|------|------|------|------|------|------|------|------|------|------|------|
| Dose                                      | SA | 1.3  | 1.4  | 1.5  | 1.6  | 1.7  | 1.8  | 1.9  | 2.0  | 2.1  | 2.2  | 2.3  |
| 200 mg/m                      |    | 250  | 275  | 300  | 325  | 350  | 350  | 375  | 400  | 425  | 450  | 450  |
| 300 mg/m                      |    | 400  | 425  | 450  | 475  | 500  | 550  | 550  | 600  | 650  | 650  | 700  |
| 400 mg/m                      |    | 500  | 550  | 600  | 650  | 700  | 700  | 750  | 800  | 850  | 900  | 900  |
| 600 mg/m                      |    | 800  | 850  | 900  | 950  | 1000 | 1100 | 1100 | 1200 | 1300 | 1300 | 1400 |
| 900 mg/m                      |    | 1200 | 1300 | 1400 | 1400 | 1500 | 1650 | 1650 | 1800 | 1950 | 1950 | 2100 |
| 1,200 mg/m                    |    | 1500 | 1650 | 1800 | 1950 | 2100 | 2100 | 2300 | 2500 | 2500 | 2750 | 2750 |

| Folinic Acid (10mg/mL, 50mg and 300mg vials) |    |     |     |     |     |     |     |     |     |     |     |     |
|----------------------------------------------|----|-----|-----|-----|-----|-----|-----|-----|-----|-----|-----|-----|
| Dose                                         | SA | 1.3 | 1.4 | 1.5 | 1.6 | 1.7 | 1.8 | 1.9 | 2.0 | 2.1 | 2.2 | 2.3 |
| 400 mg/m                         |    | 500 | 550 | 600 | 660 | 660 | 720 | 790 | 790 | 870 | 870 | 950 |

| Oxaliplatin (5mg/mL, 10mg, 50mg, 100mg vials) |    |     |     |     |     |     |     |     |     |
|-----------------------------------------------|----|-----|-----|-----|-----|-----|-----|-----|-----|
| Dose                                          | SA | 1.3 | 1.4 | 1.5 | 1.6 | 1.7 | 1.8 | 1.9 | 2.0 |
| 65 mg/m                           |    | 85  | 90  | 100 | 100 | 110 | 120 | 120 | 130 |
| 85 mg/m                           |    | 110 | 120 | 130 | 140 | 140 | 150 | 160 | 170 |
| 100 mg/m                          |    | 130 | 140 | 150 | 160 | 170 | 180 | 190 | 200 |
| 130 mg/m                          |    | 170 | 180 | 200 | 200 | 220 | 240 | 240 | 260 |

NB: CAPOX capped at 2.0

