| 5-FU (Fluorouracil)                                                                                                                                                                                                                                                                                     | 12 cycles post-op | 12 cycles during deferral of surgery | 6 cycles pre-op
6 cycles post-op |
| a For details relating to the preparation and administration of these drugs: see manufacturer's product information and refer to local guidelines.
b if the patient declines deferral of surgery post-operative systemic chemotherapy should be given i.e. as for control arm. |                   |                                      |                                     |

- In this trial the above medications will be provided, prepared and administered by the Investigator site as per local guidelines. This appendix includes recommended chemotherapy regimens. Local sites are permitted to follow their standard practice for the dosage, administration and dose adjustment of systemic chemotherapy.
- Dose banding and capping as per local guidelines is permitted for CAPOX, FOLFOX and single agent therapy as long as the delivered dose falls within  $\pm 7\%$  of the calculated dose
- Local sites are permitted to follow their local guidance for the provision of supportive medication (e.g anti-emetics)
- Assessments including but not limited to routine blood tests, pregnancy tests, physical examinations including weight, ECGs, vital signs, CEA, and renal function should be performed as per local practice prior to and during systemic treatment.

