## 2 RECOMMENDED CAPOX REGIMEN (3 WEEKLY CYCLE)

| Drug         | Dose                        | Day(s) in cycle | Administration          |
|--------------|-----------------------------|-----------------|-------------------------|
| Oxaliplatin  | 130 mg/m        | 1               | 2-6 hr i.v. infusion*   |
| Capecitabine | 1700 mg/m  /day | 1-14            | PO in two divided doses |

\* standard infusion to be given over 2hours. For patients who have a hypersensitivity reaction to oxaliplatin, it is recommended that infusion be given over 4hrs. For patients experiencing laryngopharyngeal spasm, it is recommended that infusion be given over 6hrs

Patients will be treated every 3 weeks (1 cycle) for a total of 8 cycles. As described in Table 1 patients randomized to the intervention arm in the poor response subgroup will receive 4 cycles pre-operatively and 4 cycles post-operatively.

Oxaliplatin 130mg/m^2 diluted in 250-500ml 5% dextrose will be given as an IV infusion over 2-6 hours. The maximum BSA for determining the dose of oxaliplatin and capecitabine is 2m^2.

Capecitabine will be administered as oral tablets: Capecitabine 1700mg/m^2/day (850mg/m^2 twice daily) will be administered orally for 14 days followed by 7 days' rest.

**Patients aged 75 or above** will have a reduced starting dose: Capecitabine (1300mg/m^2/day) (650mg/m^2 twice daily) given orally divided into 2 split doses in the morning and evening for 14 days followed by 7 days' rest. Oxaliplatin 100mg/m^2 will be given every 3 weeks (the maximum BSA for determining the dose of oxaliplatin and capecitabine is 2m^2).

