### 3 RECOMMENDED CAPECITABINE MONOTHERAPY REGIMEN (3 WEEKLY CYCLE)

Single agent capecitabine can be used if concomitant oxaliplatin is contraindicated.

| Drug         | Dose                                                               | Day(s) in cycle | Administration          |
|--------------|--------------------------------------------------------------------|-----------------|-------------------------|
| Capecitabine | 2000 mg/m  /day
(1000mg/m  twice daily) | 1-14            | PO in two divided doses |

**Patients aged over 75** will have a reduced starting dose: Capecitabine 1500mg/m^2/day (750mg/m^2 twice daily) given orally divided into 2 split doses in the morning and evening for 14 days followed by 7 days' rest.

**Patients aged 80 or above** will have a reduced starting dose: Capecitabine 1000mg/m^2/day (500mg/m^2 twice daily) given orally divided into 2 split doses in the morning and evening for 14 days followed by 7 days' rest.

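### Eight entries in the guidance capecitabine banding table miss the protocol's own ±7% limit, and the CAPOX-dose rows print bands above the 2.0 m² cap

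*Protocol*

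**What the plan says.** Appendix 2, section 1 (the bullets under the table of cycles by regimen and arm) lets sites band and cap doses under their own guidelines, for combination and single-agent regimens alike. The condition is that what the patient receives differs from the BSA-based dose by no more than 7% in either direction.

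Appendix 2, section 2 gives the CAPOX capecitabine starting doses: 1700 mg/m²/day, or 1300 mg/m²/day from age 75. It states a BSA cap of 2 m²: "The maximum BSA for determining the dose of oxaliplatin and capecitabine is 2m"². The cap is repeated for the older group.

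Appendix 2, section 3 covers monotherapy: "Single agent capecitabine can be used if concomitant oxaliplatin is contraindicated". The starting dose is 2000 mg/m²/day, falling to 1000 mg/m²/day from age 80. No BSA cap is stated there.

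Appendix 2, section 8 leaves banding to local practice and adds "The following dose banding tables are for guidance only". The capecitabine table, headed "Daily Dose to be Divided", has rows for 2000, 1700, 1300 and 1000 mg/m²/day, each running from 1.3 to 2.3 m². The oxaliplatin table stops at 2.0 m², and beneath it stands "NB: CAPOX capped at 2.0".

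**The concern.** A banding table printed in the same appendix as a tolerance rule should satisfy that rule, and this one does not at several band edges. A site that adopts the table as printed would, at those entries, deliver a cytotoxic dose outside the condition under which the protocol permits banding.

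The table also carries bands for the CAPOX dose levels at BSA values that the CAPOX section says must not be used to set the dose. The only reminder in section 8 sits under the oxaliplatin table, after the fluorouracil and folinic acid tables, so someone looking up capecitabine by actual BSA can miss it.

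What is at stake is consistent dosing at sites. The comparison of arms is not at stake.

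**Working it through.** **Inputs.** Tolerance ±7% (Appendix 2, section 1). CAPOX doses and the 2.0 m² cap (section 2). Monotherapy doses with no stated cap (section 3). Morning and evening doses by BSA band (section 8).

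**Formula.** Deviation = (morning + evening dose) / (mg/m²/day × BSA) − 1, at each printed 0.1 m² step.

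**Entries in use with the cap applied.** The 2000 and 1000 rows run 1.3–2.3 (11 steps each). The 1700 and 1300 rows run 1.3–2.0 (8 steps each). Total 11 + 11 + 8 + 8 = 38.

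**Entries outside ±7%.** The last column is the BSA at which the printed dose starts or stops complying: dose / (1.07 × level) for an overdose, dose / (0.93 × level) for an underdose.

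| Row (mg/m²/day) | BSA | Printed mg/day | Calculated mg/day | Deviation | Complies |
|---|---|---|---|---|---|
| 2000 | 1.4 | 3000 | 2800 | +7.1% | from 1.402 |
| 2000 | 1.9 | 3500 | 3800 | −7.9% | up to 1.882 |
| 2000 | 2.0 | 4300 | 4000 | +7.5% | from 2.009 |
| 1700 | 1.6 | 2500 | 2720 | −8.1% | up to 1.581 |
| 1700 | 1.9 | 3000 | 3230 | −7.1% | up to 1.898 |
| 1300 | 1.5 | 1800 | 1950 | −7.7% | up to 1.489 |
| 1000 | 1.4 | 1500 | 1400 | +7.1% | from 1.402 |
| 1000 | 2.0 | 2150 | 2000 | +7.5% | from 2.009 |

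Eight of 38 entries miss, by 0.1 to 1.1 percentage points. The closest complying entry is 1300 at 1.8 m²: 2500/2340 = +6.8%.

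**Sensitivity to the reading.**
- With ±7% read to the nearest whole percent, the three misses at 7.1% drop out and five remain.
- With the cap ignored and all 44 steps scored at actual BSA, ten miss. The two extra are 1700 at 2.3 m² (4300/3910 = +10.0%) and 1300 at 2.1 m² (2500/2730 = −8.4%).

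**Bands above the cap.**
- Cap applied first: 3500/3400 = +2.9% in the 1700 row and 2500/2600 = −3.8% in the 1300 row. Both comply.
- Cap overlooked: 4300/3400 = +26.5% at 2.3 m² in the 1700 row, and 3000/2600 = +15.4% at 2.2–2.3 m² in the 1300 row, relative to the capped dose.

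**Other tables.** The same formula gives largest deviations of 4.2% (fluorouracil), 4.0% (folinic acid, 790/760 before rounding 3.95%) and 3.8% (oxaliplatin). All comply.

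**The case against.** The strongest reply is that the protocol never claims ±7% for this table. The limit governs what a site delivers under its own scheme, and the table is an optional aid that leaves the site bound by the rule. This stands as a reason for low severity. It does not make the table consistent with the rule, because guidance offered to sites ought to satisfy the condition those sites must meet.

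Second, the misses are close to rounding, and the count depends on reading BSA at exact 0.1 m² points. That is fair. If printed values stand for rounded BSA, some entries scored as complying also fail: 2500 mg in the 2000 row at 1.349 m² is −7.3%. Equally, 3500 mg at 1.94 m² read as 1.9 is −9.8%, so rounding does not rescue the table. The eight are grid points and not a number of patients.

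Third, calling the upper bands redundant is an inference. Sites may follow their own practice on dosage and capping, and Appendix 2, section 6.1 lets a patient finish on a fluoropyrimidine alone after oxaliplatin toxicity. Some site might therefore use those bands uncapped. That much can be granted, but such a site would be following local practice and not this guidance. The 1700 and 1300 levels are the protocol's CAPOX starting doses, for which the cap is stated three times. The +26.5% and +15.4% figures do require a reader to overlook it.

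Finally, few patients could be affected. Five of the eight entries lie in the monotherapy rows, and planned enrolment is 90.

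**Conclusion.** The point holds, at minor severity. Eight of the 38 capecitabine entries in use fall outside the protocol's own ±7% limit, with deviations of 7.1% to 8.1%, four in each direction. The two CAPOX-dose rows continue past the 2.0 m² cap.

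The count assumes that the cap applies to the 1700 and 1300 rows only and that the calculated dose is taken at the printed BSA. At unrounded BSA, the affected band edges lie 0.002 to 0.019 m² outside the range where the printed dose complies. The protocol gives no BSA distribution, so the number of patients concerned is unknown. Because the misses run both ways and the same table serves all arms, the comparison of arms is unaffected. The primary endpoint, randomisations per month, does not depend on dosing.

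**What to change.** Re-cut the eight entries to daily totals within ±7%, using 150 and 500 mg units. One workable set:

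- 2000 row: 2650 mg at 1.4 m² (2650/2800 = −5.4%); 4000 mg at 1.9 and 2.0 m² (4000/3800 = +5.3%; 4000/4000 = 0%).
- 1700 row: 2650 mg at 1.6 m² (2650/2720 = −2.6%); 3150 mg at 1.9 m² (3150/3230 = −2.5%).
- 1300 row: 2000 mg at 1.5 m² (2000/1950 = +2.6%).
- 1000 row: 1450 mg at 1.4 m² (1450/1400 = +3.6%); 2000 mg at 2.0 m² (2000/2000 = 0%).

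End the 1700 and 1300 rows at 2.0 m² and above (3500 and 2500 mg/day), and place the CAPOX cap note beside the capecitabine table. The sponsor's oncology and pharmacy leads should set the final bands.

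The cost is one corrected guidance table and one moved note in the next amendment. The example set raises the number of bands in use from 15 to 22, a modest loss of simplicity. Recruitment, data collection and analysis are untouched.
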